## Abstract

**Objective:**

Repeated implantation failure (RIF) in *in vitro* fertilization-embryo transfer (IVF-ET) remains a challenging clinical issue. Although acupuncture is increasingly used as an adjunctive therapy for RIF patients, robust evidence supporting its efficacy in improving pregnancy outcomes is still lacking. This pilot study therefore aims to estimate effect sizes to inform sample size calculations for future definitive trials and to assess key feasibility parameters.

**Design and methods:**

This single-center, two-arm, single-blind, randomized sham-controlled trial will enroll 100 women (50 per group) with RIF aged 25~40 years. Using a parallel-group design, participants will be randomized to receive either conventional Western medicine treatment combined with acupuncture (experimental group) or the same conventional Western medicine treatment combined with sham acupuncture (control group). Acupuncture or sham acupuncture will be administered twice weekly from day 5 of the menstrual cycle until the day before embryo transfer, with a minimum of three completed sessions, targeting acupoints with standardized techniques. The primary outcome will be embryo implantation rate, and secondary outcomes will include clinical pregnancy rate and serum biomarkers (β-human chorionic gonadotropin, luteinizing hormone, progesterone, and estradiol). Safety will be monitored through adverse event reporting.

**Discussion:**

The findings of this study will provide preliminary data to guide the design of future large-scale, multicenter randomized controlled trials. Such trials would in turn generate more definitive evidence on the efficacy of acupuncture for improving pregnancy outcomes in RIF patients undergoing IVF-ET.

**Clinical trial registration:**

https://itmctr.ccebtcm.org.cn/, identifier ITMCTR2025000838

## Introduction

*In vitro* fertilization-embryo transfer (IVF-ET), as a core technique of assisted reproductive technology (ART), has helped millions of infertile patients worldwide fulfill their desire to have children. However, recurrent implantation failure (RIF), one of the major bottlenecks in IVF-ET treatment, affects approximately 10% to 15% of the patient population (1). RIF is defined as the failure to achieve a clinical pregnancy after consecutive transfers of ≥2 high-quality embryos (2). It not only imposes significant economic and psychological burdens but also potentially undermines patients’ confidence in the treatment (3). Despite the fact that recent advancements in embryo screening technologies (4) and endometrial receptivity testing (5) have notably improved the synchrony between embryos and the endometrium, the pathological mechanisms underlying RIF remain highly heterogeneous, involving multiple factors such as imbalances in the endometrial microenvironment (6), dysregulation of immune modulation at the maternal-fetal interface (7), and insufficient blood perfusion in the uterine spiral arteries (8). This complexity necessitates multi-target regulatory approaches in clinical intervention strategies for RIF.

In this context, acupuncture therapy, rooted in the holistic view and syndrome differentiation and treatment theory of traditional Chinese medicine (TCM), has gradually attracted attention. Modern research indicates that acupuncture may improve the reproductive microenvironment through multiple pathways. Acupuncture is hypothesized to optimize estrogen and progesterone secretion by regulating the hypothalamic-pituitary-ovarian axis, thus potentially prolonging endometrial receptivity (9). It may also increases uterine artery perfusion and resistance indices, thereby potentially promoting endometrial angiogenesis (10). Moreover, its proposed regulation of immune balance offers a plausible mechanism to improve embryo implantation (11). Previous clinical studies have suggested that acupuncture as an adjunct to IVF-ET may increase the clinical pregnancy rate and live birth rate in patients with RIF, and the reported improvement in embryo implantation rate has been statistically significant (12–14).

Based on this, we designed a prospective, randomized, controlled pilot trial comparing short-term acupuncture versus sham acupuncture—both combined with conventional Western medicine—in women with RIF undergoing IVF-ET. The trial employed a modified Streitberger non-invasive placebo needle as the sham acupuncture control. The primary endpoint was embryo implantation rate, with secondary endpoints including clinical pregnancy rate and changes in reproductive hormone levels. By adhering to international reporting standards, this study aims to provide relatively high-level preliminary evidence for acupuncture in RIF treatment while informing the design of future multicenter trials. If validated in subsequent confirmatory studies, this low-cost, low-risk intervention could serve as a valuable addition to comprehensive RIF management protocols.

## Methods

### Study design

This single-center, parallel-group, randomized, placebo-controlled trial will employ a patient-blinded design and be conducted at Peking University Third Hospital between December 2024 and December 2026. A total of 100 eligible participants will be enrolled and randomly allocated in a 1:1 ratio to either the experimental or control group. The trial flow is depicted in **Figure 1**. The study protocol adheres to the CONSORT (Consolidated Standards of Reporting Trials) (15) and STRICTA (Standards for Reporting Interventions in Clinical Trials of Acupuncture) (16) guidelines to ensure methodological rigor. Ethical approval has been obtained, and the trial was registered on October 21, 2024 (Registration number: ITMCTR2025000838).

**Figure 1 f1:**
[figure not shown]
Study flow diagram. IVF-ET, *in vitro* fertilization-embryo transfer; RIF, repeated implantation failure.

### Ethical considerations

All participants will provide written informed consent before randomization. Written informed consent will be obtained directly from the participants themselves. The study protocol has been approved by the ethics committees of Peking University Third Hospital (Approval number: M2024352). Findings from this trial will be submitted for publication in peer-reviewed journals following completion. Patient confidentiality will be strictly maintained, with all data anonymized and securely stored. Participants may withdraw from the study at any time without penalty.

### Participants

This study will enroll patients diagnosed with RIF who are scheduled to undergo IVF-ET at Peking University Third Hospital between December 2024 and December 2026. All participants will receive standard baseline treatment as part of routine clinical care. Potential participants expressing interest in the trial will be contacted by the research team for preliminary screening. During the initial contact, researchers will document baseline demographic and clinical characteristics, perform a comprehensive eligibility assessment using predetermined inclusion/exclusion criteria, and provide detailed study information to ensure participants can make fully informed decisions.

### Inclusion criteria

Females aged 25–40 years.Meeting the WHO diagnostic criteria for infertility (failure to achieve clinical pregnancy after ≥12 months of regular unprotected intercourse).History of ≥2 unsuccessful IVF-ET cycles with availability of ≥1 good-quality cryopreserved embryo.Normal ovarian reserve ((AMH ≥1.1 ng/mL or AFC ≥5) and regular menstrual cycles (21–35 days).Willingness to participate as evidenced by signed informed consent document.

### Exclusion criteria

Patients with active genital tract infections or systemic infections requiring treatment.Patients with significant congenital or acquired reproductive organ malformations or severe organic lesions.Patients with endocrine disorders that may affect implantation, including: (a) untreated or poorly controlled thyroid dysfunction (defined as TSH < 0.3 mIU/L or > 4.5 mIU/L); (b) hyperprolactinemia (serum prolactin > 25 ng/mL); (c) polycystic ovary syndrome (PCOS) diagnosed according to Rotterdam criteria; (d) luteal phase defect (serum progesterone < 10 ng/mL on cycle day 21).Patients with immunological or hematological disorders that may affect implantation, including: (a) autoimmune diseases; (b) inherited or acquired thrombophilia.Patients exhibiting inadequate endometrial development (thickness <6 mm or Type C pattern) on trigger day.Patients with a history of TORCH infection.Patients with a Body Mass Index (BMI) <18.5 kg/m².

### Randomization and blinding

A total of 100 eligible participants will be randomly allocated to either the experimental or control group in a 1:1 ratio using permuted block randomization. The allocation sequence will be concealed through sequentially numbered, opaque, sealed envelopes to ensure randomization integrity. This trial employs a single-blind design wherein participants will remain blinded to their group assignment throughout the trial. Practitioners administering acupuncture will necessarily be unblinded due to the inherent characteristics of the intervention. To minimize detection bias, outcome assessors (including ultrasound technicians evaluating gestational sacs and laboratory personnel analyzing hormone levels) will be strictly segregated from the acupuncture procedures and will remain blinded to group allocation. Furthermore, the statistician responsible for data analysis will also be blinded until the analysis plan is finalized and the database is locked. While performance bias cannot be entirely eliminated due to practitioner unblinding, the use of a standardized sham protocol aims to mitigate differential participant-provider interactions.

### Procedure

All participants will receive standard Western medical treatment during their IVF-ET cycles, including ovulation induction medications in the preparatory phase and luteal phase support following embryo transfer. The administration of these foundational medications cannot be fully standardized due to interpatient variability in physiological parameters. Treatment protocols are therefore individualized based on patient characteristics to maximize pregnancy success rates. To address potential confounding, the following IVF cycle characteristics will be prospectively documented for each participant: specific controlled ovarian stimulation protocol (e.g., GnRH agonist long protocol, GnRH antagonist protocol, or others), type and dosage of gonadotropins, embryo stage at transfer (cleavage stage or blastocyst), embryo quality grade, and number of embryos transferred. Acupuncture or sham acupuncture intervention will be administered twice weekly from day 5 of the menstrual cycle until the day before embryo transfer, with a minimum requirement of three completed acupuncture sessions.

### Acupuncture treatment

In accordance with TCM meridian theory, licensed acupuncturists will identify and mark the following acupoints: *Zhongwan* (RN12), *Qihai* (RN6), *Guanyuan* (RN4), *Zhongji* (RN3), bilateral *Guilai* (ST29), bilateral *Shenshu* (BL23), bilateral *Ciliao* (BL28), bilateral *Xuehai* (SP10), bilateral *Sanyinjiao* (SP6), and bilateral *Taixi* (KI6), with their precise anatomical locations detailed in **Table 1** and illustrated in **Figure 2**. Following standard aseptic protocol, all acupoints will be disinfected with 75% medical alcohol before inserting single-use sterile acupuncture needles (0.3×40 mm), then applying manual stimulation (twirling, lifting, and thrusting techniques) to elicit *de qi* sensation (characterized by soreness, numbness, distension, or heaviness), while four abdominal acupoints (*Zhongwan, Qihai, Guanyuan*, and *Zhongji*) will receive additional electroacupuncture stimulation using a G6805-1A device set at 2 Hz low-frequency continuous wave, with each acupuncture session lasting 30 minutes.

**Table 1 T1:** Location of acupoints used.

Acupoints	Locations	Needling method
*Zhongwan* (RN12)	Midline, 4 cun above the umbilicus	Straight insertion 1–1.2 cun, EA
*Qihai* (RN6)	Midline, 1.5 cun below the umbilicus	Straight insertion 1–1.2 cun, EA
*Guanyuan* (RN4)	Midline, 3 cun below the umbilicus	Straight insertion 0.8–1.2 cun, EA
*Zhongji* (RN3)	Midline, 4 cun below the umbilicus	Straight insertion 0.8–1.0 cun, EA
*Guilai* (ST29)	2 cun lateral to RN4, lower abdomen	Straight insertion 0.8–1.0 cun
*Shenshu* (BL23)	1.5 cun lateral to the spinous process of L2	Straight insertion 0.8–1.0 cun
*Ciliao* (BL28)	Sacral foramen, level with the 2nd sacral vertebra	Straight insertion 1–1.2 cun
*Xuehai* (SP10)	Medial aspect of the thigh, 2 cun above the superior border of the patella	Straight insertion 1–1.5 cun
*Sanyinjiao* (SP6)	Medial leg, 3 cun above the medial malleolus	Straight insertion 1–1.2 cun
*Taixi* (KI6)	Medial ankle, between the tendons of Achilles and flexor digitorum longus	Straight insertion 0.8–1.2 cun

EA, electroacupuncture.

**Figure 2 f2:**
[figure not shown]
Locations of acupoints.

### Sham acupuncture treatment

This trial will employ sham acupuncture as the control to verify the efficacy of acupuncture. A non-penetrating sham acupuncture protocol will be implemented using modified Streitberger placebo needles (17). During the procedure, the placebo needle will be secured to the skin at corresponding acupoints through a plastic ring. Patients will experience a pricking sensation that mimics skin penetration, while in reality, the needle tip will retract into the sleeve without piercing the skin. The sham acupuncture group will receive stimulation at the same acupoints (*Zhongwan, Qihai, Guanyuan*, and *Zhongji*) as the verum acupuncture group. Additionally, electrodes from the electroacupuncture device will be attached to these acupoints in the sham acupuncture group to maintain procedural consistency, though no electrical current will be delivered. To maintain blinding integrity, the electroacupuncture device will be activated with indicator lights illuminated and the machine will produce an audible hum, mimicking the operational state of the active treatment group.

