To rigorously evaluate the efficacy of acupuncture for RIF, this study employs sham acupuncture combined with conventional Western medicine treatment as the control group. Sham acupuncture is widely accepted in acupuncture research as a control intervention, as it effectively minimizes placebo effects associated with needle insertion (23). The selection of a sham acupuncture control rather than a usual care control reflects the explanatory nature of this trial. While a pragmatic design comparing acupuncture plus conventional treatment to conventional treatment alone might better reflect real-world practice, the current pilot study aims to isolate the specific effect of acupuncture needling from non-specific placebo effects. The use of a validated non-penetrating sham device allows for participant blinding and provides a rigorous test of the acupuncture intervention’s efficacy.

Regarding blinding, only participants will be blinded in this trial. Practitioners cannot be blinded due to the necessity of performing the acupuncture procedures (24). This study does not include long-term follow-up assessments. This design decision is based on two key considerations: 1) the transient nature of acupuncture effects is unlikely to persist for extended periods, and 2) post-treatment follow-up conducted months later would not accurately reflect the actual intervention effects. The immediate post-treatment evaluation window was therefore determined to be most appropriate for capturing the therapeutic impact of our acupuncture protocol.

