This proposed trial has several limitations that should be acknowledged. First, the absence of a formal sample size calculation means the study may be underpowered to detect statistically significant differences. Second, while participants and outcome assessors are blinded, practitioners are necessarily unblinded, which introduces a potential for performance bias. Moreover, although the sham device mimics needle insertion, the sensation of *de qi* in the verum acupuncture group or the perception of electrical stimulation may lead to partial unblinding of participants. As a pilot trial, we did not include a formal blinding credibility assessment to avoid prompting additional scrutiny that could itself bias outcomes. We acknowledge that the absence of a formal blinding evaluation represents a methodological limitation of this pilot study. To address this, future definitive trials will incorporate a validated blinding credibility questionnaire administered immediately following the intervention period to formally quantify the success of participant blinding. Third, as a single-center study, the generalizability of our findings to broader populations remains uncertain and warrants further investigation in multicenter trials. Furthermore, the non−penetrating sham acupuncture device, while effective for blinding, may not be entirely physiologically inert, as pressure and tactile stimulation at acupoints could theoretically produce mild therapeutic effects. This limitation is inherent to most sham acupuncture controls and may bias effect size estimates toward the null, reducing the observed between−group difference. Additionally, the use of a standardized acupoint prescription without TCM syndrome differentiation, while essential for ensuring internal validity and replicability in a randomized trial, may not fully reflect the individualized approach employed in real−world clinical practice. The generalizability of our findings to personalized acupuncture protocols therefore warrants cautious interpretation.

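### The sham section says sham and verum share the same acupoints but lists only 4 sites against 16 in verum; the two lists must be reconciled

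*Protocol article*

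**What the plan says.** **Verum.** The Acupuncture treatment section lists four midline points (RN12, RN6, RN4, RN3) and then "bilateral *Guilai* (ST29), bilateral *Shenshu* (BL23), bilateral *Ciliao* (BL28), bilateral *Xuehai* (SP10), bilateral *Sanyinjiao* (SP6), and bilateral *Taixi* (KI6"). Needling covers the whole list: "all acupoints will be disinfected with 75% medical alcohol before inserting single-use sterile acupuncture needles (0.3×40 mm"). The four midline points are singled out only because they "will receive additional electroacupuncture stimulation using a G6805-1A device". Table 1 gives a location and an insertion depth for all ten points and marks only those four as EA.

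**Sham.** The Sham acupuncture treatment section first says that the placebo needle is fixed over acupoints corresponding to the verum ones, without listing them. It then says that the sham group "will receive stimulation at the same acupoints (*Zhongwan, Qihai, Guanyuan*, and *Zhongji*) as the verum acupuncture group". The next sentence attaches electrodes, without current, to the points just named.

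**Purpose.** The Discussion says the pilot aims to separate the effect of needling itself from placebo effects, and adds: "The use of a validated non-penetrating sham device allows for participant blinding and provides a rigorous test". The Sample size section says the estimated difference will feed the power calculation of a later multicentre trial.

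**Blinding check.** The limitations paragraph expects that de qi or felt current may partly unblind participants. It says "we did not include a formal blinding credibility assessment to avoid prompting additional scrutiny that could itself bias outcomes", names this as a limitation, and plans a questionnaire for the definitive trials.

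**The concern.** A sham-controlled contrast can be read as a needling effect only if the two procedures match in everything except penetration and current. The sham section asserts that match and then gives a list that does not deliver it. A practitioner working from this text could apply sham needles at 4 sites or at 16 and claim to have followed it either way.

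If the short list is literal, sham women have no device contact on the back, sacrum, thighs, legs or ankles, nor at the lateral lower-abdominal points, while verum women do. The between-group difference would then combine penetration and current with the number of sites, the body regions exposed and the amount of handling. The limitations paragraph itself allows that pressure and touch at acupoints may have a mild effect. If so, a sham with fewer contact sites delivers less of it. That paragraph considers only a bias toward the null from a sham that is not inert, and does not consider this imbalance. The Randomization and blinding section also relies on a standardized sham to limit differential interaction with unblinded practitioners, which presupposes that the sham is fixed unambiguously.

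**Working it through.** The check is a count, followed by a reading of the two sections side by side.

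**Verum sites** (Acupuncture treatment section and Table 1)
- Midline points RN12, RN6, RN4, RN3: 4 points × 1 site = 4 sites.
- Bilateral points ST29, BL23, BL28, SP10, SP6, KI6: 6 points × 2 sites = 12 sites.
- Total: 4 + 6 = 10 named points; 4 + 12 = 16 sites.

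**Sham sites listed** (Sham acupuncture treatment section)
- RN12, RN6, RN4, RN3: 4 named points, 4 sites.

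**Without a stated sham counterpart**
- 10 − 4 = 6 named points; 16 − 4 = 12 sites, which is 12/16 = 75% of the verum sites.
- By Table 1, 2 of the 12 are on the lower abdomen (ST29). The other 10 are at the back, sacrum, thigh, leg and ankle.

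**Two readings of the sham section**
- *Full list.* The unlisted reference to corresponding points, and the claim of sameness with verum, both point to all 16 sites. The verum section uses the same four-name parenthesis to identify the electroacupuncture points, so the sham parenthesis may have been meant for the electrode sites only.
- *Short list.* The parenthesis is attached to the sentence about stimulation. The electrode sentence follows as an addition and refers back to those points. Read grammatically, the four names define where the sham is given.

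Neither reading makes the text consistent: the first leaves a wrong or misplaced list, the second a false claim of sameness.

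**Optional blinding item: what 50 women per arm could show**
- Per-arm index = proportion guessing correctly (p1) − proportion guessing incorrectly (p2).
- Variance = [p1(1 − p1) + p2(1 − p2) + 2·p1·p2]/n.
- With index 0, no don't-know answers and n = 50, p1 = p2 = 0.5, so the variance is (0.25 + 0.25 + 0.50)/50 = 0.02.
- 95% half-width = 1.96 × √0.02 = 0.28.

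This is coarse, but enough to reveal gross unblinding. It assumes an answer from all 50 women in the arm.

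**The case against.** The strongest reply is that the sham section, read as a whole, intends all verum points and that the parenthesis is an editing slip. A condensed article may also leave site-by-site sham detail to a fuller protocol that is not shown. The first part may well be right, which is why this point alleges a contradiction and no more. The second does not remove it: the article does give a list, and the list disagrees with the sentence that contains it.

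A reader might go further and infer three things that the document does not support.
- *That 12 sites go untreated in the sham arm, or that women have already been treated unequally.* Nothing reports what was delivered, and the reference to corresponding acupoints points the other way.
- *That four needles against 16 unblinds participants.* In a parallel-group trial each woman sees only her own procedure. Fewer needles reveals allocation only to someone who knows the other arm's list, and the document does not say that participants do.
- *That leaving out a blinding check is an error.* It is a disclosed choice with a stated reason. The reason is weak when gestational sacs are read by blinded ultrasound staff, and it sits awkwardly with the plan to ask the question in the next trial. But that same blinded reading also limits how far a participant's belief could distort the primary outcome. Reasonable statisticians differ here.

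**Conclusion.** The contradiction between the two intervention sections is real: 10 named points and 16 sites in verum, 4 points and 4 sites listed for sham, and 6 points (12 sites) with no described counterpart. These counts need no assumption.

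The consequence depends on which reading is meant. If the parenthesis marks only electrode sites, the defect is one of wording and the design stands. If it is literal, the contrast mixes needling with number of sites, regions and contact, and cannot serve the Discussion's aim. The effect estimate passed to the definitive trial would carry the same mixture. How large that distortion would be in terms of implantation rate cannot be calculated from the document. The point should be settled because the sham definition determines what the pilot estimates. The absent blinding check supports only an optional suggestion.

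**What to change.** Reconcile the Acupuncture treatment and Sham acupuncture treatment sections so that the claim of shared acupoints is true of the lists given. State for each verum site how the sham mirrors it: a non-penetrating needle at every site needled in verum, and dummy electrodes at the sites that receive electroacupuncture. If the parenthesis was meant for the electrode sites, move it to the electrode sentence. Which acupoints belong in the prescription is for the investigators and is not at issue here.

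Because recruitment is stated to run from December 2024 to December 2026, check what has been delivered so far. If any women prove to have had a shorter sham list, record which procedure each received.

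Optionally, add one treatment-guess item (verum, sham, don't know) after the last session and before transfer, and report a per-arm index alongside recruitment, retention and adherence.

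The cost is a protocol wording change, possibly more placebo needles per sham session, and a one-line form if the optional item is taken up.
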